## Appendix A

### Study Covariates

#### 1. Patient parameters

- a. Age
- b. Race
- c. Surgeon ID and tier
- d. MRI Fusion Biopsy used
- e. Preop and postop Gleason score
- f. Preop PSA
- g. Preop SHIM score
- h. Preop use of erectile aid
- i. Prostate volume
- j. Number of masses
- k. Mass size
- l. Extracapsular extension
- m. Tumor location
- n. Tumor orientation
- o. PIRADS score
- p. Perineural invasion
- q. SV invasion
- r. Risk category
- s. Clinical stage
- t. Oncologic stage
- u. Number of positive biopsy cores
- v. Use of erectile aids (pre and postoperatively)

#### 2. Surgical technique

- a. Node dissection template, if performed
- b. Assistant port used
- c. SV dissection approach

#### 3. Operative Parameters

- a. Total operative time
- b. Blood Loss (cc)
- c. Conversion to open (y/n)
- d. Operative complication (y/n)
- a. Hospital stay (days)
- b. Mortality (y/n)
- c. Readmission (y/n)

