- f. **3D Model Creation and Delivery:** MRI scans will be deidentified and sent in Digital Imaging and Communications in Medicine (DICOM) format to Ceevra, Inc., where a patient-specific 3D model for each intervention patient will be created. The Prostate Imaging-Reporting and Data System (PIRADS) score will be used to identify and label prostate lesions. In addition, the biopsy report, will be used to create a patient-specific pathology map that will be included in the model to assist the surgeon in understanding the location of biopsy-proven cancer within the prostate. Models will be delivered to a mobile application on the surgeon's smartphone (Ceevra Reveal) and viewed as described above. In addition, the surgeon may view the model picture-in-picture on the robotic console screen using a video cable connection between the surgeon's smartphone and the surgical robot.
- g. **Outcomes Measures and Covariates:** The primary outcome measure is oncologic outcomes after RALP. This outcome will be measured at three time points: immediately postoperative, short term, and a final assessment when oncologic and functional outcomes have reached a steady state. Oncologic outcomes will be measured as margin status (positive or negative), PSA (linear and detectable/undetectable) at the initial assessment (which in most cases is three months postoperatively but may occur any time between 3 and 6 months), and PSA ( $>0.1$ ) at the final assessment (to be collected after 18 months but no later than 24 months). Additionally, any use of androgen deprivation therapy or radiation therapy will be captured at 24 months as an adverse oncologic outcome.
- Secondary outcomes are the urinary and sexual function of the patient, measured at the same three time points as above. For urinary function, this is bladder neck sparing (yes or no), measured immediately postoperatively, and incontinence pads per day, measured at both 3-6 months and 18-24 months postoperatively. For sexual function, this is nerve sparing (none, left, right, or bilateral), measured immediately postoperatively, followed by SHIM score, measured at both 3-6 months and 18-24 months postoperatively.
- Demographic data, disease-specific, surgery-specific, and surgeon-specific covariates will be collected from the medical record as well, see Appendix A.

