- h. **Sample Size:** Sample size was calculated using prior data, including previous trials using 3D models in robotic partial nephrectomy. Previously we noted an effect size of 0.44 regarding the difference of outcome measures between 3D

model-aided and control groups. To account for multiple endpoints, we raised the sample size by 15%. Using the above method and paired t-test, the sample size of 90 (45 per arm) provided 80% power to detect clinically significant differences in our primary outcome measures with  $\alpha=0.05$ .

- i. **Statistical analysis:** Initial analysis will compare baseline characteristics between cases performed with (intervention) or without (control) models involved in preoperative planning. A two-sample t-test will be employed to compare means between groups and Chi-Square test or Fisher's exact test to assess the association between categorical variables. For outcome measures, the appropriate test will be used as described above to compare groups. To mitigate type I error due to multiple comparisons, and if the randomization yields balanced cohorts, a Bonferroni correction may be utilized for the primary and secondary outcomes. If randomization yields groups with statistically or clinically significant differences, adjusted differences between groups will be studied using a linear mixed model to regress the endpoint variables on covariates listed above, or the logistic mixed model, as appropriate.

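### Perioperative harm is listed only as covariates, is not planned to be compared by arm, and has no common collection period for complication, readmission and mortality

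*Combined protocol and SAP*

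**What the plan says.** Section IV.g defines what the trial measures as outcomes. It opens with "The primary outcome measure is oncologic outcomes after RALP": margin status, PSA at 3-6 months and PSA at 18-24 months. It adds that "any use of androgen deprivation therapy or radiation therapy will be captured at 24 months as an adverse oncologic outcome". The secondary outcomes are urinary and sexual function: bladder neck sparing, pads per day, nerve sparing and SHIM score.

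Everything else is introduced by one sentence: "Demographic data, disease-specific, surgery-specific, and surgeon-specific covariates will be collected from the medical record as well, see Appendix A". Appendix A is headed "Study Covariates". Its section 3, Operative Parameters, lists total operative time, blood loss, "Conversion to open (y/n", "Operative complication (y/n", hospital stay, mortality and "Readmission (y/n". No period of observation is attached to any of them.

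Section IV.i plans two comparisons between the arms. The first is of baseline characteristics. The second is stated as "For outcome measures, the appropriate test will be used as described above to compare groups". If the arms turn out unbalanced, the endpoints are to be regressed on the covariates in a linear or logistic mixed model.

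**The concern.** The 3D model is used to plan the operation and is available during it. The Appendix B survey asks whether it led the surgeon to change the plan, and whether anything in it was missing or looked inaccurate. An effect on operating time, bleeding or complications is therefore plausible in either direction. These are also the data a reader would want beside any gain in margins or function.

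Followed as written, IV.i produces no table of these items by arm. A benefit could be reported while longer operations or more complications in the same arm stay out of view.

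Two further weaknesses follow from treating the items as covariates:

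- They arise after randomisation, yet the plan allows endpoints to be regressed on covariates. If that includes section 3 of Appendix A, the model adjusts for possible effects of the intervention.
- Complication, readmission and mortality are yes/no items with no stated period. IV.d says that the staff who extract data from the medical record know the allocation. An open-ended item recorded by unblinded staff leaves room for judgement that a stated window would reduce.

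**Working it through.** The plan gives no figure for perioperative harm, so there is none to reproduce. The check has two parts.

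**1. Reading the sections together**

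| Item | Status | Time point stated | Compared by arm under IV.i |
|---|---|---|---|
| Margin status | Primary outcome | Immediately postoperative | Yes |
| PSA | Primary outcome | 3-6 and 18-24 months | Yes |
| Androgen deprivation or radiation | Adverse oncologic outcome | 24 months | Yes |
| Pads per day, SHIM | Secondary outcomes | 3-6 and 18-24 months | Yes |
| Operative time, blood loss, conversion, hospital stay | Covariates | None, but bounded by their nature | No |
| Complication, readmission, mortality | Covariates | None | No |

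The section 3 items are neither baseline characteristics, since they arise after randomisation, nor outcome measures under IV.g. They fall outside both comparisons. Their only possible analytic role is as regressors.

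**2. What a comparison by arm could show at this size**

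Input: 45 per arm (IV.h), taken as given. The documents state no event rates, so the rates below are assumptions shown as a range.

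*No events in one arm.* Exact upper limit:

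- one-sided 95%: 1 − 0.05^(1/45) = 0.064, or 6.4%
- two-sided 95%: 1 − 0.025^(1/45) = 0.079, or 7.9%

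*One illustrative difference*, 10/45 against 5/45:

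- difference = 0.222 − 0.111 = 0.111
- SE = √(0.222 × 0.778/45 + 0.111 × 0.889/45) = 0.078
- 95% CI = 0.111 ± 1.96 × 0.078, about −4 to +26 percentage points

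*Range of assumed rates.* Half-width of the 95% CI when both arms have rate p is 1.96 × √(2p(1 − p)/45). Power to detect a doubling (two-sided 0.05) is Φ[(|p₂ − p₁|√45 − 1.96√(2p̄(1 − p̄))) / √(p₁(1 − p₁) + p₂(1 − p₂))], where p̄ is the mean of p₁ and p₂. Fisher's exact power was found by enumeration.

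| Control rate | Half-width, equal rates | Power for doubling, normal | Power for doubling, Fisher | n per arm for 80% power (normal) |
|---|---|---|---|---|
| 5% | 9.0 points | 14% | 6% | 435 |
| 10% | 12.4 points | 26% | 18% | 199 |
| 15% | 14.8 points | 40% | 30% | 121 |

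The normal approximation is rough at the 5% rate, where about two events per arm are expected (0.05 × 45 = 2.25).

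*Continuous items.* For operative time, blood loss and hospital stay, the half-width of the 95% CI for a difference in means is about 1.96 × √(2/45) = 0.41 standard deviations. The documents give no standard deviations.

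These figures support reporting estimates with intervals. They do not support hypothesis tests of harm or a conclusion about safety.

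**The case against.** The strongest reply is that the plan does compare harms. A reader might infer from the covariate list that no adverse result is set out by arm. IV.g and IV.i do not support that. Positive margin, PSA failure, later androgen deprivation or radiation, pads and SHIM score are all outcomes with time points. Cancer left at the margin, an obvious risk of altered nerve or bladder neck sparing, is a primary outcome. This part of the reply stands, and the point is confined to perioperative harm.

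Other limits also stand:

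- Conversion, operative time, blood loss and hospital stay end with the operation or the admission and need no follow-up window. The missing period concerns complication, readmission and mortality only.
- A reader might infer that sites will count events over different periods, or that a complication after discharge is excluded. The text shows neither. It leaves the period and the scope unspecified.
- The 3-6 month assessment is not the first outcome time point. IV.g has an immediately postoperative one before it.
- Section III is not in the text supplied, so absence is judged without it.

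It can also be said that the items are recorded and the allocation is known, so a table by arm could be made without redesign, and the primary result is untouched. That limits the seriousness of the point but does not answer it. A table that nobody has planned need not appear, and a window chosen after the data are seen is weaker than one stated beforehand.

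**Conclusion.** The point holds for perioperative harm. On the text supplied, the seven items in Appendix A section 3 have covariate status only, and IV.i plans no comparison of them by arm. Three of them (complication, readmission, mortality) have no stated collection period, in a multi-institution trial where the extractors know the arm. That they might be used as regressors depends on reading the covariates in IV.i as including all of Appendix A, which IV.g invites.

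A reader might go further and conclude that the omission is what prevents the trial from saying whether the model is safe. The numbers do not support that. At 45 per arm, no events leaves a two-sided upper limit of 7.9%. A doubling from an assumed 5% or 10% would be detected with at most 14% or 26% power. The trial could not establish safety even with the table. What is lost is that perioperative harm would not be visible by arm beside the benefits. This should be corrected, but it does not threaten the primary analysis.

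**What to change.** - **IV.g and Appendix A:** move section 3 of Appendix A out of the covariates and name its items as safety outcomes. State that these post-randomisation items will not be used as regressors in the IV.i models.
- **Collection period:** state one common window after surgery for complication, readmission and death, applied at every site. Its length is for the sponsor to set. One that ends by the 3-6 month assessment would fit the existing schedule; since that assessment may fall at 3 months, the window would have to close by then to be complete for every man.
- **IV.i:** report all seven items by randomised arm, with counts or means, differences and 95% confidence intervals (exact methods where counts are small). Label them descriptive, place them outside the multiplicity correction, and make no claim that safety is established.
- **Optional:** ask each man at the 3-6 month assessment about care received elsewhere. Record extraction may miss such care, and patients are blinded under IV.d. This would be new data collection, because section VIII draws case data from the health record and the surveys, and the only surveys described are of surgeons.

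Without the optional question, the cost is protocol wording and one extra table from data already to be collected. The downside is wide intervals, which must be presented as such.

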**Appendix B**  
**Surgeon Pre- and Postoperative Survey**

Preoperative Survey (after viewing MRI but before viewing model)

- 1) Do you plan to perform nerve sparing (none, right, left, bilateral)
- 2) Do you plan to perform bladder neck preservation (yes, no)

Preoperative Survey (after viewing MRI and model)

- 1) Do you plan to perform nerve sparing (none, right, left, bilateral)
- 2) Do you plan to perform bladder neck preservation (yes, no)

Postoperative Survey

- 1) How would you rate your ability to see and define the area of cancer in the MRI (Likert)
- 2) How would you rate your ability to see and understand the relationship between the mass and the adjacent structures in the MRI (Likert)
- 3) How would you rate your ability to see and define the area of cancer in the model (Likert)
- 4) How would you rate your ability to see and understand the relationship between the mass and the adjacent structures in the model (Likert)
- 5) Were there any anatomical structures that you were able to see (or see better) in the model as opposed to the MRI (yes, no)
- 6) If answer to the question above is yes, please explain (free text)
- 7) Were there any structures or details that you could see in the source MRI that were either missing from, or appeared to be inaccurate in the model (yes, no)
- 8) If answer to the question above is yes, please explain (free text)
- 9) Did you modify your preoperative plan in any way as a result of what you saw in the model (yes, no)
- 10) If answer to the question above is yes, please describe how (free text)
- 11) Did you perform nerve sparing (yes, no)
- 12) How much did the model aid you in performing nerve sparing, if performed (Likert)
- 13) Did you perform bladder neck preservation (yes, no)
- 14) How much did the model aid you in performing nerve sparing, if performed (Likert)

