**IV. STUDY DESIGN.**

- a. **Trial Design:** A multi-institution, randomized, single-blind clinical trial
  - b. **Participants and Exclusion Criteria:** Eligible subjects identified from the medical record will be those who are 1) scheduled to undergo RALP surgery, 2) willing to consent to the surgery being performed by one of the surgeons participating in the study, and 3) willing to be assigned by randomization to one of the two groups in the study. Exclusion criteria are 1) prior prostate surgery, ablation, radiation, or androgen deprivation therapy, 2) lack of 3 Tesla or 1.5 Tesla with endorectal coil preoperative MRI imaging, and 3) inability to give informed consent.
  - c. **Randomization:** Each case will be assigned to one of the two preparation methods by a randomization procedure that is stratified by surgeon. Each surgeon-specific randomization schedule will be prepared using permuted blocks of size 2; i.e., each 2-patient block will be some permutation of {VR-aided, Control}. Thus, each surgeon's cases will be randomized in a 1:1 ratio. Use of permuted blocks thus avoids any confounding of preparation method with temporal trends (e.g., trend due to a learning curve.)
- Sequentially numbered opaque sealed envelopes (SNOSEs) will be prepared for each individual surgeon. Each envelope will contain the treatment assignment for one case (intervention or control). There will be an equal number of envelopes containing intervention assignments and control assignments; the total number of envelopes provided to each surgeon will be determined based on the surgeon's historical/anticipated case volume. The treatment code will remain concealed inside the envelope until the moment the case is ready to be prepared.

- d. **Blinding:** Patients, personnel gathering data from the video review, and statistician will be blinded. Control and intervention groups identifiers will be known only to the research personnel opening the sealed envelope for random group assignment and extracting patient data from the electronic medical record.
- e. **Intervention:** For intervention cases, surgeons will be provided with a 3D model to view (a) prior to the operation in addition to the MRI and biopsy results and (b) during the operation in addition to the MRI. For control cases, surgeons will view only the MRI and biopsy results prior to the operation and during the operation itself.

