## V. SURGEON SURVEYS

- a. **Pre- and Postoperative Surgeon Surveys** will be administered to assess various factors, such as surgeon change in operative plan, model quality, and utility of the models. The preoperative survey will be administered for intervention cases only. The preoperative survey will be administered after viewing the model but before the operation, and the postoperative survey will be administered after the operation. These surveys are described in Appendix B

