## VI. RESEARCHERS AND RESPONSIBILITIES

- a. **Principal Investigator (PI):** One PI from each participating Site.
  - i. Overall Site point person for study.
  - ii. Coordinates support for study with other Site participants, including Research Coordinator and surgeon users.
  - iii. Primary interface with the Site's IRB.
- b. **Research Coordinator ("RC").** One RC from each participating site. A researcher, fellow, resident or student identified and recruited by the PI. Key activities:
  - i. Identify upcoming cases to be included in the study and assign cases to control group or intervention group using block randomization.
  - ii. Identify, collect and manage:
    1. The MRIs from which the models will be created
    2. Data regarding Control Cases ("**Control Case Data**") and intervention cases ("**Intervention Case Data**")
  - iii. Deidentify each source MRI using deidentifying software (or ensures that Radiology deidentifies the image prior to delivery to the RC); deliver the deidentified image to Ceevra along with a unique identifier.
  - iv. Coordinate with surgeon users to ensure that both the model and the underlying MRI are reviewed prior to intervention cases.
  - v. Assist with administration of the surgeon surveys

- 130           **c. Surgeon Users.** Estimated between one and eight surgeon users (inclusive of  
131           the PI) from each site. Key activities:
- 132               i. Oversee receipt of informed consents from their patients participating in  
133               the study.
  - 134               ii. Provide the mobile phone used for viewing the models
  - 135               iii. Before each intervention case, review the source MRI and then review  
136               the associated model for purposes of case planning.
  - 137               iv. Participate in surgeon surveys.
- 138       **VII. MODEL CREATION KEY PERSONNEL**
- 139           **a. [name], CEO.** Overall Ceevra point person for study.
  - 140           **b. [name], CTO.**
    - 141               i. Oversees the creation of the models from the MRIs.
    - 142               ii. Oversees Ceevra software application and infrastructure.
    - 143               iii. Primary point of contact for user technical support issues.
- 144       **VIII. DATA COLLECTION AND SECURITY PLAN**
- 145           **a. Protocol for Case Data.** Case data will be extracted from the site's EHR system,  
146           and the surveys. It will be tracked via two files:

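### In intervention cases the MRI and the model are rated side by side and only after surgery, so the survey's MRI-versus-model comparison is open to hindsight and contrast bias

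*Combined protocol and SAP*

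**What the plan says.** Section V.a introduces surgeon surveys meant to capture, among other things, changes of operative plan and the quality and usefulness of the models. It limits the preoperative survey to intervention cases and places it between viewing the model and operating. Of the other survey it says that "the postoperative survey will be administered after the operation", without stating whether control cases receive it.

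Appendix B gives the content:

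- A first preoperative form, headed "Preoperative Survey (after viewing MRI but before viewing model"), asks only about planned nerve sparing and planned bladder neck preservation. Its first item is "Do you plan to perform nerve sparing (none, right, left, bilateral").
- A second preoperative form, completed once the model has also been viewed, repeats those two questions.
- The Postoperative Survey opens with four Likert ratings. Item 1 is "How would you rate your ability to see and define the area of cancer in the MRI (Likert") and item 3 is "How would you rate your ability to see and define the area of cancer in the model (Likert"). Items 2 and 4 are the matching pair on how the mass relates to neighbouring structures.

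On exposure, IV.e says of the intervention arm that "surgeons will be provided with a 3D model to view (a) prior to the operation in addition to the MRI and biopsy results". The same paragraph makes the model available during surgery as well. IV.f allows picture-in-picture display on the robotic console. VI.c fixes the order of review: "Before each intervention case, review the source MRI and then review" the matching model.

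**The concern.** Items 1-4 are the survey's only paired, scaled ratings of MRI against model, so a reader will compare them. When the surgeon scores the MRI in an intervention case, three things have already happened: the model has been studied, it may have been used at the console, and the anatomy has been seen directly. The MRI score is then a recollection, given on the same page as the model score in almost identical wording.

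If items 3-4 score higher than items 1-2, the difference could reflect a better depiction of the tumour, a contrast effect, hindsight from the operation, or a mixture. The form cannot separate these. What is at stake is any statement about model quality or utility drawn from the ratings. An MRI rating given before the model was seen also cannot be recovered afterwards, so a change helps only cases not yet done.

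**Working it through.** The documents state no figure for these ratings: no scale length, expected score, standard deviation or planned test. There is nothing to reproduce, and the check is one of timing and content.

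**Sequence in an intervention case**

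| Step | Source | What is recorded |
|---|---|---|
| 1. Surgeon reviews MRI | VI.c, IV.e | First preoperative form: nerve-sparing and bladder-neck plans. No MRI rating |
| 2. Surgeon reviews model | VI.c, IV.e | Second preoperative form: the same two plans. No model rating |
| 3. Operation, with MRI and model available | IV.e, IV.f | No survey |
| 4. After the operation | V.a | Items 1-2 (MRI) and 3-4 (model), together |

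A moment with MRI exposure alone exists at step 1, and a form exists for it. The first MRI rating comes at step 4, after both model and operation. The plan questions are asked at steps 1 and 2, so the protocol already separates before-model from after-model answers for the operative plan, but not for the image ratings.

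**What the postoperative difference contains.** Let R and M be the ratings that the surgeon would give to the MRI and the model if each were free of these influences. Let b_R and b_M be the shifts caused by rating late and side by side. Then

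observed difference = (M − R) + (b_M − b_R).

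The documents fix neither b_R nor b_M. Contrast with the model could lower the MRI score (b_R < 0), which favours the model. Seeing the real anatomy could expose faults in the model (b_M < 0), which works against it. As illustration only, assume a 5-point scale and a shift of 0.25 to 1 point in one of the two ratings:

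- MRI score lowered, model score unchanged: b_M − b_R = 0 − (−0.25) = +0.25, up to 0 − (−1) = +1.
- Model score lowered, MRI score unchanged: b_M − b_R = −0.25 − 0 = −0.25, down to −1 − 0 = −1.

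With no shift, or with equal shifts, the bias is zero. Under these assumptions it can therefore lie anywhere from −1 to +1, and its sign is not determined.

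**Extent.** IV.h plans 45 per arm. All 45 intervention cases are affected on four items each: 45 × 4 = 180 ratings.

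**Control cases.** IV.e states: "For control cases, surgeons will view only the MRI and biopsy results prior to the operation and during the operation itself". There is no model to rate, so the paired comparison exists only in the intervention arm.

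**Bearing on the trial's outcomes.** IV.g lists oncologic, urinary and sexual-function measures. The survey ratings are not among them, and IV.i plans no test of items 1-2 against items 3-4.

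**Timing of the preoperative survey.** V.a places it after the model has been viewed. Appendix B has one stage before the model and one after. The two do not agree, and the first stage is the one that a clean MRI rating needs.

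**The case against.** The strongest reply is that postoperative timing has a purpose. Both MRI and model are in use during the operation, and only a rating given afterwards can reflect that use and the anatomy actually found. Moving the model items wholly before surgery would lose this information. That stands, and it is why the items should be added before surgery, not moved.

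Second, preoperative rating would not remove all bias. The model is always viewed second, by a surgeon who is not among those blinded under IV.d. The first preoperative form is also used only in intervention cases, so the surgeon knows that a model is coming. This too stands. The gain is narrower: the MRI rating would precede exposure to that patient's model, and neither rating would follow the operation.

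Third, these are opinions outside the primary and secondary outcomes, and the plan already measures change of operative plan at suitable times. That limits the importance of the point, but model quality and utility remain declared survey purposes.

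Stronger readings are tempting, and the documents do not support them:

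- A reader might infer that the ratings are certainly distorted in the model's favour by some number of Likert points. The documents show exposure to bias, not its size or sign.
- A reader might infer that MRI ratings differ systematically between arms because control surgeons rate without a model for contrast. V.a does not say that control cases receive the postoperative survey. Randomization is also within surgeon in blocks of 2 (IV.c), so surgeons may bring model experience to their control cases.
- A reader might infer that the survey is meant to prove better understanding of anatomy with the model than with MRI. No section makes that claim.

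**Conclusion.** The point holds as a minor one about design. In every intervention case, the only MRI ratings are collected after the operation, after the model has been used, and next to the model ratings. The resulting MRI-versus-model comparison is open to hindsight and contrast bias of unknown size and direction. It affects four items in each of the 45 planned intervention cases and leaves the randomized comparison of primary and secondary outcomes untouched.

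This conclusion rests on two assumptions: that the forms are used as Appendix B lays them out, and that someone will read items 1-2 against items 3-4, which their parallel wording invites but IV.i does not plan.

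**What to change.** 1. Add items 1-2 to the existing preoperative form completed before the model is viewed, and items 3-4 to the existing preoperative form completed after it.
2. State that any MRI-versus-model comparison uses these preoperative ratings, paired within case, and state the length of the Likert scale.
3. Keep items 1-4 on the Postoperative Survey as a separate rating that covers intraoperative use, and report it as such.
4. Align V.a with Appendix B, so that both describe one preoperative stage before the model and one after it.
5. State in V.a whether control cases complete the Postoperative Survey and, if so, which items apply.

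The cost is two added questions on each of two existing forms. That makes four repeated questions per intervention case, or 4 × 45 = 180 extra responses at the planned size, at about a minute per form (a judgement; the documents give no timing). No new form or visit is needed. Order and expectation effects remain and should be acknowledged when the ratings are reported.

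### Appendix B postoperative item 14 repeats item 12, so the survey has no rating of the model's help with bladder neck preservation

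*Combined protocol and SAP*

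**What the plan says.** Section V states that the surgeon surveys assess factors "such as surgeon change in operative plan, model quality, and utility of the models", and refers to Appendix B for their content.

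The postoperative survey in Appendix B ends with four items on the two operative steps:

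- Item 11: "11) Did you perform nerve sparing (yes, no"
- Item 12: "12) How much did the model aid you in performing nerve sparing, if performed (Likert"
- Item 13: "13) Did you perform bladder neck preservation (yes, no"
- Item 14: "14) How much did the model aid you in performing nerve sparing, if performed (Likert"

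Both preoperative surveys, one before and one after the model is viewed, ask for the plan on the same two steps. The nerve-sparing plan is asked with side: "1) Do you plan to perform nerve sparing (none, right, left, bilateral".

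Section IV.g lists the steps as performed among the secondary outcomes: "bladder neck sparing (yes or no), measured immediately postoperatively" and "nerve sparing (none, left, right, or bilateral), measured immediately postoperatively".

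**The concern.** Appendix B is the data collection form itself. A wording slip there goes straight into the data unless someone corrects it before use. If surgeons answer item 14 as printed, the study holds two copies of the nerve-sparing rating and none for the bladder neck. If some answer it as printed and others read it in the light of item 13, the responses mix two questions and cannot be separated in analysis. Either way, one of the two operative steps that the survey covers has no usable rating of the model's usefulness. A surgeon's impression of a particular case would not normally be found in the medical record; asking for it later would rely on recall.

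**Working it through.** The plan gives no figure to reproduce, and the point rests on no calculation of power or error rate. The check is a comparison of the items.

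**Step 1: the two pairs side by side.**

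| Step | Was it done? | How much did the model help? |
|---|---|---|
| Nerve sparing | Item 11, yes/no | Item 12, Likert, on nerve sparing |
| Bladder neck preservation | Item 13, yes/no | Item 14, Likert, again on nerve sparing |

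Apart from their numbers, items 12 and 14 are identical. The lower right cell is where a bladder neck rating would be expected, and it is empty in substance.

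**Step 2: is the rating collected elsewhere?**

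- Items 1 to 8 concern what could be seen in the MRI and in the model. They do not ask about help with an operative step.
- Items 9 and 10 ask whether the model led to a change of plan, with free text. The bladder neck could appear there, but only if the plan changed and the surgeon chose to mention it.
- The bladder neck outcome in Section IV.g and item 13 both record whether the step was done, not whether the model helped.

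The number of structured items rating the model's help with bladder neck preservation is therefore 0.

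**Step 3: how many cases.** Section IV.h plans 45 patients per arm. The rating makes sense only where a model was supplied and the step was performed, so the number of affected cases lies between 0 and 45. The documents give no rate of bladder neck preservation that would narrow this.

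**Step 4: the response scale of item 11.** Item 11 has 2 levels; the preoperative nerve-sparing item and the Section IV.g outcome each have 4. The question is whether the side is lost to the trial.

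- Planned side: in both preoperative surveys, at 4 levels, for intervention cases (Section V restricts the preoperative survey to these).
- Side performed: in the Section IV.g secondary outcome, at 4 levels.
- Link: Section VIII.a draws case data from the health record and the surveys, and the data file carries a unique identifier.

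Planned and performed side can therefore be compared case by case without item 11. Only the postoperative survey taken alone lacks the side.

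**The case against.** The strongest reply is that this is an evident slip in an exploratory opinion item. The surveys are neither primary nor secondary outcomes, and nothing in the sample size or statistical analysis sections uses them. Whether the bladder neck was preserved is recorded twice, in the Section IV.g outcome and in item 13, so that secondary outcome is safe. Surgeons could also be asked afterwards, within the limits of recall. All of this stands, and it sets the severity. It does not remove the defect: the form as printed does not ask the question, and its position after item 13 makes the answers ambiguous.

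A reader might go further and infer from item 11 that side-specific departures from the nerve-sparing plan go unrecorded. Four levels allow 4 × 3 = 12 ordered changes from planned to performed, and the 3 × 2 = 6 changes among left, right and bilateral all end in a yes on item 11. The documents do not support treating those 6 as lost. The preoperative item gives the planned side, the secondary outcome gives the side performed, and the two can be linked. A change of plan prompted by the model is seen directly by comparing the two preoperative surveys, with items 9 and 10 in addition.

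One small loose end remains. Section IV.g does not name the source of the nerve-sparing outcome, and Section VIII.a allows case data to come from the surveys. A yes/no item cannot supply a four-level outcome, so the outcome as defined has to be recorded elsewhere; saying where would settle it.

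**Conclusion.** The point holds for item 14. The form duplicates one rating and omits the other, so the model's usefulness for bladder neck preservation could not be validly reported for intervention cases in which that step was performed (at most 45). This assumes that the survey is used as printed and that items 13 and 14 were meant as a pair like items 11 and 12, which the layout strongly suggests.

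For item 11 there is only an inconsistency of response levels. No loss of side-specific information should be claimed, provided the nerve-sparing outcome is collected at the four levels that Section IV.g defines.

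Severity is minor. No primary or secondary outcome analysis, between-group comparison, error rate or sample size is affected.

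**What to change.** In Appendix B, postoperative item 14, replace nerve sparing with bladder neck preservation and keep the rest of the item, including the condition that the step was performed and the Likert scale.

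Optionally, give item 11 the same four responses as the preoperative item (none, right, left, bilateral), or add a line stating that the side performed is taken from the Section IV.g secondary outcome.

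The cost is one change of wording, plus one optional edit, with no added items and no added burden on surgeons. If the form is already in use, record the date of the change and do not analyse earlier item 14 responses as bladder neck ratings.
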